#### Baseline Questionnaire (t0)

In addition to the scales mentioned, the baseline questionnaire includes questions on sociodemographic characteristics of both the IC and the patient, as well as potential associated factors. Table 2 gives an overview of the included items and scales. All baseline data were collected without planned missing values. The German baseline questionnaire is displayed in Multimedia Appendix 4.

**Table 2. T2:** Included items and scales in the baseline questionnaire for assessing potential associated factors on psychological burden and supportive care needs.

Questionnaire or scale	Description	Analyses
Sociodemographics		
Single items	For example, age and gender of the informal caregiver and the patient.	Single-item analyses.
Socioeconomic status (SES; Winkler Index [56,57])	The Winkler Index is a composite indicator score for assessing the socioeconomic status of a person, taking into account the highest school qualification, highest professional qualification, occupational position, and monthly household net income. Classifications are low, medium, and high SES.	Syntax-based calculation of a score and allocation to a social class: lower class, middle class, and upper class.
Family functioning		
Brief Assessment of General Family Functioning Scale (BAFFS) [58,59]	The BAFFS is the three 3-item ultra-short version of the General Functioning Scale of the Family Assessment Device. Each item is answered on a 4-point Likert scale ranging from 1=strongly agree to 4=strongly disagree.	Calculation and analysis of a sum score (ranging from 3 to 12). Suggested cutoffs are 3‐6=satisfaction with family functioning and 7‐12=distress with family functioning [58].
Preparedness for the role of being an informal caregiver		
Self-developed items, based on the Preparedness for Caregiving Scale [60]	“All in all: How well prepared do you currently feel in your role as an informal caregiver of a loved one with a terminal illness?” This item is answered on a 5-point Likert scale ranging from 1=not good at all to 5=very well. “Is there anything you would like to be better prepared for in your role?” with free-text option.	Single-item analyses.
State of health of the patient and conditions of care		
Self-developed items^a^	Time since the initial diagnosis. Patients’ overall state of health over the last week. Global item, answered on a 7-point Likert scale ranging from 1=very poor to 7=excellent. Patient’s overall quality of life during the last week. Global item, answered on a 7-point Likert scale ranging from 1=very poor to 7=excellent. Previous use of SPC^b^. Previous location of care.	Single-item analyses.

a Self-developed items are displayed in Multimedia Appendix 5.

b SPC: specialist palliative care.

#### Follow-Up Questionnaires (t1-t10) and Implementation of the Planned Missing Data Design

To minimize the burden of the repeated data collection on the ICs, a design with planned missing data—a multiform design—is implemented for all follow-up questionnaires. As summarized by Little and Rhemtulla [31], this design reduces the number of items each participant answers by randomly splitting the total set of items across several forms. The participants are then randomly assigned to one of the forms, answering only the subset of items [31]. Previous research indicates that collecting data with this design leads to similar results compared to complete data designs and can improve validity by reducing participant burden and fatigue, lowering rates of unplanned missing data, and improving efficiency [31,32,61,62]. The multiform design used in this study is based on the work of Rhemtulla and Hancock [32]. A fixed block X consists of 14 items included in every follow-up questionnaire: current care situation of the patient (including an option to report death), all items from the CAREPAL-8, the 1-item analog scale of the DT, a free-text item about recent events that have influenced the burden and needs of the IC, as well as date and mode (with or without assistance) of questionnaire completion. The items from the following scales—GAD-7, PHQ-9, SF-8, OSLO-3, and FIN—are randomly assigned to 6 blocks (A-F), each containing 7‐8 items. The number of blocks was determined as a function of the time that ICs can be expected to spend completing the follow-up questionnaires (approximately 15‐20 minutes) and the number of items. Each follow-up questionnaire includes the fixed block X and 2 different blocks of A-F. Taking all combinations into account, this results in 15 different follow-up questionnaires. Table 3 gives an overview of the questionnaire composition.

**Table 3. T3:** Composition of the follow-up questionnaires.

Block	Items	Follow-up questionnaire number														
		1	2	3	4	5	6	7	8	9	10	11	12	13	14	15
X fixed	For example, current care situation (patient), CAREPAL-8^a^, DT^b^	✓	✓	✓	✓	✓	✓	✓	✓	✓	✓	✓	✓	✓	✓	✓
A randomized	GAD-7^c^ i4^d^; PHQ-9^e^ i2; OSLO-3^f^ i1, i2; FIN^g^ i5, i9, i15, i18	✓	✓	✓	✓	✓										
B randomized	GAD-7 i6; PHQ-9 i7; SF-8^h^ i3*;* OSLO-3 i3; FIN i4, i6, i12, i13	✓					✓	✓	✓	✓						
C randomized	GAD-7 i2; PHQ-9 i6, i9; SF-8 i1, i6; FIN i7, i14, i20		✓				✓				✓	✓	✓			
D randomized	GAD-7 i5; PHQ-9 i3, i5; SF-8 i4, i7; FIN i3, i8, i19			✓				✓			✓			✓	✓	
E randomized	GAD-7 i1, i7; PHQ-9 i1, i4*;* FIN i2, i10, i11*,* i17				✓				✓			✓		✓		✓
F randomized	GAD-7 i3; PHQ-9 i8; SF-8 i2, i5, i8; FIN i1, i16					✓				✓			✓		✓	✓

a CAREPAL-8: 8-Item Screening Tool for Family Caregiver Burden in Palliative Care.

b DT: Distress Thermometer.

c GAD-7: Generalized Anxiety Disorder 7-item scale (items 1-7).

d i: item.

e PHQ-9: Patient Health Questionnaire Depression Module (items 1-9).

f OSLO-3: Oslo Social Support Scale (items 1-3).

g FIN: Family Inventory of Needs (items 1-20).

h SF-8: Short-Form Health Survey (items 1-8).

The questionnaires are randomly distributed at each follow-up measurement point for every IC. The randomization is realized as follows: randomized sets of follow-up questionnaires are prepared for each study center, with each set containing an equal number of all 15 questionnaires (eg, each questionnaire is counted 5 times, resulting in sets of 5*15=75 questionnaires in total). If a study center collects data in more than 1 setting (eg, palliative care ward and specialist palliative home care team), each setting is provided with a separate set of randomized questionnaires to avoid imbalances. For every measurement point, each IC must receive a questionnaire from this predetermined set. Distributing a set of prepared questionnaires for multiple time points to one IC is not allowed to avoid imbalances that may occur if several questionnaires remain unanswered. The version (questionnaire number 1‐15) of the randomly allocated questionnaire is documented for each IC and measurement point. The implementation of the planned missing data design ensures that each follow-up questionnaire contains only half of the total items—29 to 30 instead of all 61—thereby relevantly reducing its length.

### Statistical Analyses

At first, we will conduct a descriptive analysis; we will report mean and SD for continuous variables and absolute and relative frequencies for categorical variables.

#### Longitudinal Assessment of Burdens and Needs

The cohort will be examined to identify groups with similar trajectories using growth mixture modeling (GMM) techniques [63]. More precisely, latent class growth analysis will be used to determine appropriate grouping structures among ICs. We will use the Bayesian information criterion as a relative measure of model performance and derive the most suitable number of trajectories from this. Factors associated with membership in these groups will be identified using a multinomial, multivariable regression model. Because the baseline assessment period was extended from the initially planned 3 days to 7 days, sensitivity analyses will be conducted using the 3-day subsample. As planned missing values are by design missing completely at random, we will use a multiple imputation approach to impute the missing data. Any additional unplanned missing values, potentially not missing completely at random, will be imputed in a further step if necessary. More precisely, first, we impute missing data at baseline on scale level after calculation of scales. In this step, only unplanned missing data exists. We only take this step for the data we use in the GMM. Second, we impute planned missing data on item level, set replaced unplanned missing data to missing data again, and then, calculate the scales and impute the unplanned missing data on scale level. The imputation model consists of all baseline and follow-up variables. Any missing values resulting from the patient’s death will be set to missing data again. We will use a joint modeling approach with a Weibull distribution of event times to account for missing data due to the patient’s death.

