With this study, we aim, first, to record longitudinal data on the burden and supportive care needs of ICs in the course of SPC. The data will be analyzed with regard to joint trajectories of burden and supportive care needs. If specific trajectories can be identified, their characteristics, frequencies, as well as associated factors will be examined. Additionally, comparisons between different settings of SPC will be conducted. Second, we seek to validate the new multidimensional screening tool CAREPAL-8.

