### Study Design and Setting

This 3-year cohort study on the psychosocial burden and supportive care needs of ICs in SPC in Germany implements a prospective, multicenter, longitudinal design with up to 11 measurement points using self-report questionnaires. To minimize the burden of repeated data collection in this vulnerable population, a planned missing data design is implemented for all follow-up measurement points [31,32]. This methodological approach allows item allocation between participants, resulting in shorter questionnaires and reduced completion time per participant [32]. Further details on the implementation of the planned missing data design used in this study are provided in the Follow-Up Questionnaires (t1-t10) and Implementation of the Planned Missing Data Design section.

A total of 16 university hospitals and nonacademic facilities across Germany, hereinafter referred to as study centers, are participating in data collection. The consortium management lies with the University Medical Center Hamburg-Eppendorf, hereinafter referred to as the leading center. The study centers are located in 7 federal states of Germany, representing both urban and rural areas. Three common settings of SPC in Germany are involved: (1) palliative care wards, (2) multiprofessional SPC teams in hospitals, and (3) specialist palliative home care teams. According to the typology suggested by Wikert et al [33], all 3 settings employ multiprofessional staff, most of them with palliative care qualification. Palliative care wards are independent hospital wards, while multiprofessional SPC teams in hospitals operate hospital-wide. Specialist palliative home care teams can either be affiliated with a hospital or operate independently. Some of the study centers include more than 1 setting so that data collection is performed on 11 palliative care wards, in 5 multiprofessional SPC teams in hospitals, and in 8 specialist palliative home care teams. An overview of the 16 study centers, including their locations and the SPC settings they cover, is provided in Multimedia Appendix 3.

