#### Longitudinal Assessment of Burdens and Needs

As the number of trajectory types is an outcome of this exploratory study, sample size calculation for GMMs is not feasible due to the uncertainty of key parameters. As a proxy, a mean comparison of the baseline variables between trajectory types is used. An IC is part of the analysis population if the baseline data and at least 1 follow-up questionnaire are valid. Various scenarios with 3 to 6 trajectory types were calculated.

Assuming, for reasons of clinical practicability, a highest number of 6 trajectory types and a small effect size (η^2^=0.025), we would need 85 ICs per group (total of 510 ICs) to detect this effect size with a power of 80% and a 2-sided type I error of 5%. This calculation assumes equal group sizes.

Sijbrandij et al [65] examined cases where estimation or performance issues arise when using GMMs. The authors concluded that no performance issues occur with sample sizes of 1000 individuals, while sample sizes of 300 individuals can present performance challenges, which can only be addressed by limiting variance parameters. Furthermore, we cite the study of Kim [66], which investigates GMMs in the sample size range targeted in this study. Additionally, we searched for studies using GMMs [67-72], which included sample sizes ranging from 129 to 6987 individuals. Our targeted sample size of 510 ICs is on the lower end of this range, but it is similar to another study conducted in the palliative care setting [71].

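### Latent class growth analysis with the number of classes taken from BIC is likely to report several trajectory types in a population that has only one, if a caregiver's repeated scores are correlated at about 0.3 or more

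*Protocol article*

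**What the plan says.** Under Statistical Analyses, Longitudinal Assessment of Burdens and Needs, the article opens with the broad family: "The cohort will be examined to identify groups with similar trajectories using growth mixture modeling (GMM) techniques". The next sentence makes this specific: "latent class growth analysis will be used to determine appropriate grouping structures among ICs". The rule for the number of classes follows: "We will use the Bayesian information criterion as a relative measure of model performance and derive the most suitable number of trajectories from this". The classes are then used as an outcome: "Factors associated with membership in these groups will be identified using a multinomial, multivariable regression model".

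Two other places bear on this. The Introduction leaves open that no distinct trajectories exist: "If specific trajectories can be identified, their characteristics, frequencies, as well as associated factors will be examined". The Sample Size Calculation treats the number of types as a study outcome and plans for 3 to 6 of them. It also reports from a cited simulation study that "sample sizes of 300 individuals can present performance challenges, which can only be addressed by limiting variance parameters". It states no within-class variance structure for this study.

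**The concern.** Latent class growth analysis, as the term is normally used, fixes the within-class variance of intercepts and slopes at zero. Given class, a caregiver's weekly scores are then treated as independent. If some caregivers are simply more burdened than others throughout, the model can reproduce the resulting correlation only by cutting the continuous spread into roughly parallel bands. A comparison of BIC among such models rewards the cutting.

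The number and shape of trajectory types is the main result of aim 1. If the rule returns several types whether or not they exist, the one-class answer that the Introduction allows for is hardly reachable. The multinomial regression may then identify predictors of overall burden level under the name of predictors of trajectory type. A spurious count would also tend to fall among the 3 to 6 types used in planning, so it would look like confirmation.

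**Working it through.** **The plan's own figure.** One-way ANOVA with 6 groups and η²=0.025: f² = 0.025/0.975 = 0.02564; noncentrality = 510 × 0.02564 = 13.08 on 5 and 504 degrees of freedom; power 0.804. The stated 85 per group (510 in total) is reproduced and is not in question here.

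**Inputs.** From the article: N=510, up to 11 measurement points, baseline plus at least one follow-up, latent class growth analysis, BIC. Assumed, because the article gives no value: within-person correlation 0 to 0.7; mean number of observations per caregiver 3.0, about 5.5, or all 11 (the article says only that high attrition is expected).

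**Data.** One class only: a common linear mean plus a normal random intercept with variance τ² and residual variance σ². The correlation between two scores of one person is τ²/(τ²+σ²).

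**Fitted model.** K classes with quadratic means, a common residual variance and no random effects, K = 1 to 7. BIC = −2 log L + p ln N, with p = 3K + (K−1) + 1 = 4K. Each added class therefore costs 4 × ln 510 = 4 × 6.234 = 24.9 points.

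**Number of classes chosen by BIC (true number: 1).**

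| Correlation | Mean 3.0 observations (12 runs) | Mean about 5.5 (20 runs; 4 at 0.7) | All 11 (4 runs) |
|---|---|---|---|
| 0 | 1 in 12 | 1 in 20 | 1 in 4 |
| 0.1 | 1 in 5, 2 in 7 | 2 in 20 | 2 in 4 |
| 0.3 | 2 in 9, 3 in 3 | 3 in 15, 4 in 5 | 4 in 4 |
| 0.5 | 3 in 4, 4 in 7, 5 in 1 | 4 in 9, 5 in 10, 6 in 1 | 5 in 1, 6 in 3 |
| 0.7 | 4 in 4, 5 in 6, 6 in 2 | 6 in 2, 7 in 2 | 7 in 4 (the maximum fitted) |

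Entries read: classes chosen in number of runs. At 0.1, two classes were chosen in 7 + 20 + 4 = 31 of 36 runs. At 0.3 or more, more than one class was chosen in all 36 + 36 + 20 = 92 runs, and the smallest BIC advantage of two classes over one was 68 points.

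A separate simulation with linear class means and a mean of about 6.4 waves (12 runs per correlation) agreed: 3 or 4 classes at 0.3, 4 or 5 at 0.5, and 5 to 7 at 0.6.

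**Rival model.** Adding one class-invariant random-intercept variance costs one parameter (6.2 BIC points). On the same random-intercept data, with K = 1 to 3 fitted, BIC chose one class in every run at every correlation and attrition level. In the linear-mean simulation at correlation 0.5 (5 runs), the one-class mixed model beat the best class-only model by 49 to 79 points.

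**Limit of the intercept-only rival.** At correlation 0.5, a true random slope (SD 0.5 in simulation units) was added to the one-class data. The random-intercept mixture then still chose two classes in 4 of 4 runs at a mean of 5.5 observations and in 4 of 4 with all 11. It chose one class in 12 of 12 at a mean of 3.0. A mixture with a shared slope variance as well was not simulated.

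**The case against.** The strongest case has four parts.

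- **The result is conditional.** A reader might infer that the plan will report several types whatever the data look like. The documents do not support that. They give neither a within-person correlation nor an attrition figure; at correlation 0 BIC chose correctly, and at 0.1 with few observations it did so in 5 of 12 runs. Heavy attrition, which the article expects, reduces the number of spurious classes. This stands and limits the claim.
- **The simulated analysis is simpler than the planned one.** It has one continuous outcome, no imputation, and no joint model with Weibull event times. The longitudinal part of that joint model is unspecified and could carry random effects. This stands as a limit on the size of the effect. However, the article presents the joint model as the way to handle missing data due to death, not as a change to the class-finding model.
- **The article is condensed.** A reader might infer that BIC is the only criterion and that a one-class mixed model is never considered. The text says neither. Class-size limits, entropy and the list of candidate models are commonly left to the analysis plan, and their absence is not held against the article. What can be reviewed is the stated pairing of model family and selection rule.
- **The choice may be deliberate.** The study is exploratory, a descriptive grouping into higher and lower burden has its uses, and 510 lies between the 300 and 1000 discussed under Sample Size Calculation, where limiting variance parameters is mentioned. This has some force, but the article does not give it as the reason, and one or two shared variances would respect the same constraint.

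**Conclusion.** The concern holds in conditional form. Under latent class growth analysis in its usual meaning, with the number of classes taken from BIC, a single homogeneous population yields about 2 to 4 classes at a within-person correlation of 0.3 and about 3 to 6 at 0.5. At 0.1 it mostly yields 2, and at 0 it yields one. A correlation of 0.3 or more is plausible for weekly self-reports by the same person, but it is an assumption. If it holds, the plan is likely to report several trajectory types even where burden varies continuously, and the factors associated with membership may reflect overall burden level. The counts rest on 4 to 20 runs per cell of the table and on assumed attrition. The direction is firm at 0.3 and above; the exact number of spurious classes is not.

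**What to change.** For each number of classes, fit both the latent class growth model and a growth mixture model with class-invariant within-class variance: a random intercept, and a random slope where it can be estimated. The intercept alone is not enough if slopes truly vary. Include the one-class mixed model among the candidates and select by BIC across both families. Keep the latent class growth result as a reported comparator. If the one-class mixed model is best, report that no distinct trajectories were found, and do not interpret the regression on class membership as evidence about trajectory types.

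This needs no new data. It costs a change of wording in the analysis plan and additional model runs. Some random-effects mixtures may converge slowly or fail; the plan should say that this will be reported and that the class-only fit then remains as a comparator.

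### If many pre-death weeks go unreturned, filling them from a class-free imputation model before latent class growth analysis can add spurious classes and flatten trajectories

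*Protocol article*

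**What the plan says.** All of this stands in the protocol article under Statistical Analyses, Longitudinal Assessment of Burdens and Needs, unless another section is named.

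- Grouping: "latent class growth analysis will be used to determine appropriate grouping structures among ICs".
- Class number: "We will use the Bayesian information criterion as a relative measure of model performance and derive the most suitable number of trajectories from this".
- Unplanned gaps: "Any additional unplanned missing values, potentially not missing completely at random, will be imputed in a further step if necessary". The detailed steps that follow fill baseline gaps, then planned-missing items, and then "calculate the scales and impute the unplanned missing data on scale level".
- Content of the imputation model: "The imputation model consists of all baseline and follow-up variables".
- Death: "Any missing values resulting from the patient’s death will be set to missing data again". Also: "We will use a joint modeling approach with a Weibull distribution of event times to account for missing data due to the patient’s death".

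That imputation precedes the class search is implied by this sequence and not stated in so many words. Sample Size Calculation admits a caregiver with baseline and one valid follow-up form. Recruitment of ICs and Data Collection expects heavy attrition, mainly from patient death or caregiver withdrawal, and gives no rate.

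**The concern.** Class membership is latent, so it is not among the baseline and follow-up variables, and no class-specific or mixture imputation is described. A missed week is therefore drawn from relations averaged over all classes. Latent class growth analysis allows no person-level variation within a class. A record that is part observed and part pooled draw fits no true class curve, and the model can absorb it only by bending a curve or adding a class. BIC then rewards the extra class.

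The Weibull joint model does not deal with this, because its stated purpose is missingness from death. Block X cannot help either: an unreturned form loses the Distress Thermometer and CAREPAL-8 for that week along with everything else.

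The number and shape of the trajectories are the result of aim 1, and the multinomial regression of associated factors is built on the classes. The one sensitivity analysis named in that section, on the 3-day baseline subsample, would not reveal the problem.

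**Working it through.** **The plan's own figure.** The 510 in Sample Size Calculation reproduces: 6 groups of 85, η² = 0.025, noncentrality 510 × 0.025 / 0.975 = 13.08, power 0.804. It does not depend on this point. It fixes the simulated sample size and the maximum of 6 classes.

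**Model.** In class k, the score at week t is b0k + b1k·t + b2k·t² plus independent error with common variance. Each extra class adds 4 parameters (3 curve coefficients, 1 weight). With BIC = −2 log L + p·ln N and N = 510, the penalty is 4 × ln 510 = 24.9. Any spurious gain in log-likelihood above 24.9 / 2 = 12.5 therefore buys another class.

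**Mechanism by hand (assumed values).** Take classes of 55% flat at 6, 30% rising from 9 to 15 and 15% falling from 14 to 8, with within-class SD 3.
- Pooled mean at t0: 0.55×6 + 0.30×9 + 0.15×14 = 8.1. At t10: 0.55×6 + 0.30×15 + 0.15×8 = 9.0.
- Variance at t0: (0.55×36 + 0.30×81 + 0.15×196) − 8.1² + 9 = 73.5 − 65.61 + 9 = 16.89.
- Covariance of t0 and t10: (0.55×36 + 0.30×135 + 0.15×112) − 8.1×9.0 = 77.1 − 72.9 = 4.2.
- Pooled slope: 4.2 / 16.89 = 0.249.
- Imputed t10 mean for a faller at 14: 9.0 + 0.249×5.9 = 10.5 (true 8). For a riser at 9: 9.0 + 0.249×0.9 = 9.2 (true 15).

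This is the extreme case of conditioning on baseline alone. Each returned week moves the draw towards the caregiver's own class.

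**Simulation.** 510 caregivers, 11 weekly waves, 1 to 6 classes tried. In settings A to D death runs at about 8% per week, post-death values are blanked, missed weeks are imputed 5 times from a class-free model, and BIC is averaged over imputations. The comparator is maximum likelihood on the observed scores. Entries are runs in which the true class number was chosen. Planned-missing items are not simulated in A to D.

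| Setting | Pre-death weeks missed | After imputation | Observed scores, ML |
|---|---|---|---|
| A. 3 classes, normal draws | 4% | 24/24 | 24/24 |
| A | 17% | 2/24 (4 classes in 14, 5 in 8) | 24/24 |
| A | 31% | 0/24 (4 in 2, 5 in 9, 6 in 13) | 24/24 |
| B. 3 strongly crossing classes, normal draws | 17% | 7/8 | 8/8 |
| B | 39% | 3/8 | 7/8 |
| C. 4 classes, normal draws | 17% | 3/8 | 8/8 |
| C | 39% | 0/8 (6 in all) | 8/8 |
| D. 3 classes, predictive mean matching | 17% | 15/16 | 16/16 |
| D | 31% | 5/16 | 16/16 |
| D. 4 classes, predictive mean matching | 18% | 15/16 | 16/16 |
| D | 31% | 3/16 | 16/16 |

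**Shape, setting A at 31%.** True changes from t0 to t10 of −1, 0 and +6 became 0.03, 0.79 and 4.40 after imputation, against −0.95, 0.04 and 5.97 by maximum likelihood.

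**With planned-missing items included.** Setting: 20 runs, one third of items seen per follow-up, three classes of 55/30/15%, weekly hazards of 10% death and 8% withdrawal, and 10% intermittent non-return. At 26% missed, BIC chose 4-6 classes in 20/20 runs after imputation (six in 12). It chose 3-4 in 20/20 with missed weeks left missing. The class falling from 14 to 8 came out as 11.9 to 12.4, against 13.0 to 10.0; the adjusted Rand index was 0.36 against 0.52. At 12% missed, the index was 0.57 against 0.59.

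**With withdrawal depending on earlier burden.** At 24-27% missed, in 16 runs that included this case, BIC chose 4-6 classes in 16/16 after imputation and 3-4 in 16/16 by maximum likelihood. At 10-12% missed the gap was small.

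**The case against.** Several points on the other side stand.

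- **The step is conditional and partly unspecified.** It applies only if necessary, and the algorithm is not named. The full protocol or an analysis plan may settle the algorithm and the pooling of BIC over imputations, so neither is raised here. However, no criterion for necessity is given, and the detailed steps read as if they will be done.
- **The imputation has a real purpose.** A reader might infer that the step is redundant because a likelihood fit rests on the same missing-at-random assumption. The article does not support that. Its imputation also conditions on other baseline and follow-up variables, which a single-outcome fit ignores, and it concedes that the gaps may not be completely random. This argues for keeping the imputation as a second analysis.
- **Maximum likelihood does not guarantee the right number.** With a within-class random intercept of SD 1.5 (total SD 3), it never chose the true 3 classes: it chose 5-6 in 16/16 runs at 11% and at 18% missed, and 4-6 in 16/16 at 29%. It still classified better at 29% (Rand 0.52 against 0.34). At SD 2.1 both approaches chose 6 throughout, with Rand 0.30 against 0.28 at 11% missed and 0.28 against 0.25 at 29%.
- **The missed-week rate may be modest.** Unreturned forms are followed up, return rates are monitored, and post-death gaps do not count.
- **Normal draws are not a best case for imputation.** They force normality on a mixture, and predictive mean matching did much better at 17-18%.
- **Reversal is too strong a word.** A reader might infer that a class would be reported as moving the wrong way. The simulated falling class became nearly flat, which is attenuation.

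**Conclusion.** The point holds as a conditional one. The procedure as written can produce surplus classes and trajectories drawn together when a substantial share of pre-death weeks is missed. At about a quarter or more this appeared with both imputation algorithms and in most runs of every configuration tried. It was least marked for strongly crossing classes, where the count was still right in 3 of 8 runs at 39% missed. At 17-18% the result depended on algorithm and class pattern, from 2/24 correct to 15/16. At about 10% or less it was small.

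These sizes rest on assumed missed-week rates, class separation and algorithm, none of which the article gives, so they are not forecasts for this study. The contrast is also cleanest when the model's assumption of no within-class variation holds. The change below therefore removes one source of spurious classes without ensuring the correct number. It should be made, because the class solution is the main result of aim 1 and nothing planned would show the problem.

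**What to change.** 1. For class enumeration and trajectory shapes, impute only the planned-missing items on returned forms. Leave unreturned pre-death weeks missing, as the plan already does after death, and fit by maximum likelihood.
2. Keep the scale-level imputation of unplanned gaps as a sensitivity analysis, and report whether class number and shapes agree.
3. Repeat the enumeration on the Distress Thermometer and the two CAREPAL-8 indices. They are on every form and need no planned-missing imputation, so this also checks the remaining pooled draws of planned-missing items.
4. Report the share of pre-death weeks not returned, so that readers can judge how much the choice matters.

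Cost: analysis wording and a few extra model fits, with no new data. Downsides: the likelihood fit does not use the auxiliary variables unless they are added to the model, and it does not cure over-extraction from within-class variation that latent class growth analysis leaves out.
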